**Fig. 2 Fig2:**
[figure not shown]
Study flow chart

### Sample size {14}

To analyse cluster-randomised trials, specific constraints must be followed, as individuals within a cluster are assumed to be more similar compared to individuals from different clusters. In order to detect significant effects, the sample size of the trial must be adjusted. This so-called clustering effect (1 + (*m*-1)×*p* [*m* = average number of subjects per cluster; *p* = intraclass correlation coefficient (ICC)]) resulted in an estimated *N* = 1795. For *m*, we assumed an average of 80 within an entire grade as the average class size in Germany varies nationwide (21.2–30.4 students per class), and the ICC was estimated quite conservatively at approximately 0.05 [70] on the basis of the primary outcome. Hence, a clustering effect of 4.95 was determined. Assuming a small effect size (Cohens *d* = 0.2) in universal prevention based on previous studies [71], with a significance level alpha = 0.05 and a power = 0.9, g*power suggests a total of *N* = 306 [72]. Considering the clustering effect, we have to multiply this by 4.95, reaching an overall *N* = 1515. Assuming a dropout rate of 25% due to moving out of the area, sickness, or other reasons, we must add another 379, leading to the final *N* = 1894.

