## Methods: participants, interventions, and outcomes

### Study setting {9}

The study will be conducted in the Federal states of Mecklenburg-West Pomerania, Bavaria, and Hesse [59]. Due to the broad geographical sample and the wide age range of 12–18 years, we will be able to obtain a well-generalisable epidemiological overview. The number of participating schools or classes cannot be predicted at this stage, for the following two reasons: (1) the pandemic has dramatically increased the stress and workload in schools, which is associated with less participation in non-school projects. (2) We are focusing on direct contact with teachers, school psychologists, and school social workers to bring the program to their schools, which can lead to more time required for recruitment.

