### Recruitment {15}

The recruitment will take place in autumn 2022. Schools are the most appropriate setting for universal prevention for the following reasons: (1) An adolescent’s life is mostly played out at school, (2) compulsory school attendance provides the opportunity to reach a large number of adolescents, and (3) there is evidence that students are more likely to accept such programmes within school than during their free time. The School Boards will help us to get in touch with eligible schools. *LessStress* targets classes from the 6th to 12th grade at public and private schools. Any school principal or council expressing an interest can officially register for potential participation via mail. In a next step, further information material regarding the study will be sent out if required. If schools agree to participate, a letter of consent has to be signed, stating how many grades and classes will participate in *LessStress*.

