## Assignment of interventions: allocation

### Sequence generation {16a}

Participating schools will be randomly assigned to one of the two groups using Microsoft Excel. The randomisation will be carried out on the school level following a 1:1 allocation ratio. This enables interference between the IG and WL to be avoided.

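### The design effect of 4.95 takes one grade of 80 students as the cluster, but whole schools of unfixed size are randomised, so 1894 students alone do not secure 90% power

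*Protocol article*

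**What the plan says.** Sample size {14} gives the design effect as 1 + (m − 1) × ICC and defines m as the mean number of subjects per cluster. For m, "we assumed an average of 80 within an entire grade". On the correlation, "the ICC was estimated quite conservatively at approximately 0.05", without saying whether this refers to class, grade or school. Then: "Hence, a clustering effect of 4.95 was determined". The base N of 306 is multiplied by 4.95 to give 1515, and 25% is added for dropout to give 1894.

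The randomised unit is different. Sequence generation {16a} says: "The randomisation will be carried out on the school level following a 1:1 allocation ratio". The Randomisation paragraph under Trial design {8} says the same.

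How many students one school contributes is left open. Recruitment {15} targets grades 6 to 12 and has each school sign a letter "stating how many grades and classes will participate in *LessStress". Study setting {9} adds: "The number of participating schools or classes cannot be predicted at this stage". The statistical methods section {20a} lists school and grade as separate levels of clustering.

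**The concern.** All students in a school share one allocation, so the variance of the treatment comparison depends on the number of students per school and on how alike students of one school are. A grade is the right cluster for the formula only if each school contributes about one grade of participants. Nothing in the protocol makes that so.

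Precision in such a trial comes mainly from the number of schools. A target counted only in students can be met by many small schools or by a few large ones, and these carry very different amounts of information. The Discussion relies on the adjusted sample size to make even small effects visible. The section on the data monitoring committee {21a} says the trial cannot be modified once the intervention group has started. The point therefore has to be settled before randomisation.

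**Working it through.** **Inputs from Sample size {14}:** m = 80, ICC = 0.05, base N = 306, alpha 0.05, power 0.90, 25% added for dropout.

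**Reproducing the plan.** 1 + (80 − 1) × 0.05 = 4.95. 306 × 4.95 = 1514.7, so 1515. 1515 × 1.25 = 1893.75, so 1894. All three figures reproduce. The planned effective sample is 1515 / 4.95 = 306.

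The starting value of 306 does not follow from d = 0.2, alpha 0.05 and power 0.90: a two-sided comparison of two means needs 1052 in total. That is a separate problem. Here 306 is kept and taken to give power 0.90, so that only the cluster size changes.

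**Smaller schools.** With 25 participants per school, 1 + 24 × 0.05 = 2.2. With 50, 1 + 49 × 0.05 = 3.45. Both lie below 4.95.

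**Several grades per school.** Take 0.05 as the correlation within a grade and ρ as the correlation between students in different grades of one school. For g grades of 80:

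DE = 1 + 79 × 0.05 + 80 × (g − 1) × ρ

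For g = 2 this is 4.95 + 80ρ, and for g = 3 it is 4.95 + 160ρ. The values of ρ and g are assumptions, since the protocol gives neither.

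**Unequal school sizes.** With mean 80 and an assumed coefficient of variation (CV) of 0.5: 1 + ((1 + 0.25) × 80 − 1) × 0.05 = 5.95.

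**Power.** Effective N = 1515 / DE, and power = Φ(3.242 × √(effective N / 306) − 1.960), where 3.242 = 1.960 + 1.282 (two-sided 0.05, power 0.90).

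| Assumption | DE | Effective N | Power |
|---|---|---|---|
| One grade, equal sizes (plan) | 4.95 | 306 | 0.90 |
| Mean 80, size CV 0.5 | 5.95 | 255 | 0.84 |
| Two grades, ρ = 0.01 | 5.75 | 263 | 0.85 |
| Two grades, ρ = 0.03 | 7.35 | 206 | 0.76 |
| Two grades, ρ = 0.05 (upper value) | 8.95 | 169 | 0.67 |
| Three grades, ρ = 0.05 (upper value) | 12.95 | 117 | 0.52 |

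These are normal approximations. They make no allowance for the few degrees of freedom left when there are few schools.

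**Students against schools.** At ICC 0.05 and base 306, the analysed schools needed are 306 × DE / m: 18.9 at m = 80, 17.1 at m = 160 and 16.5 at m = 240. The requirement in schools hardly moves. Yet 1894 students come from 1894 / 80 = 23.7 schools, 1894 / 160 = 11.8 or 1894 / 240 = 7.9, so the student count alone does not control what matters.

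**The case against.** **Direction.** A school may enter a single class, and participation needs consent from guardians and students, so participants per school may fall well below enrolment. Two grades at an assumed 50% consent would give exactly 80. This stands: the text does not show that schools will exceed 80.

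**ICC.** The protocol calls 0.05 conservative, and correlation across a whole school may be weaker than within a grade. At an assumed ICC of 0.03, 160 students per school give 1 + 159 × 0.03 = 5.77, about 17% above 4.95. This stands as a limit on size: 8.95 and 12.95 are upper values. It does not restore the plan. With two full grades, 4.95 holds only if a single school-wide ICC falls to 3.95 / 159 = 0.025, or if 0.05 applies within grades and students in different grades are uncorrelated. The protocol states neither.

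**Disclosure.** The protocol openly says that the number of schools cannot be predicted, and an article may leave detail to a fuller document. The missing count is therefore not an oversight. The mismatch between a grade-sized m and school-level randomisation, however, is in the stated calculation itself, and uncertainty about school numbers is a reason to set a minimum.

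**Conclusion.** The mismatch is certain from the text: m is the size of a grade, schools are randomised, and participants per school are not fixed. The stated 90% power therefore holds only if schools contribute about 80 participants each, of similar size, and the other inputs are right.

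The size of the error is conditional. If schools enter two full grades, power falls to about 0.85 to 0.76 for an assumed between-grade correlation of 0.01 to 0.03, and to about 0.67 at the upper value of 0.05. If schools enter only one or two classes, the plan is more than covered on this point.

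Two stronger readings are tempting but not supported. A reader might infer that 4.95 simply understates the clustering; the recruitment rule allows schools small enough for it to be too high. A reader might also set 1894 / 4.95 = 383 against the effective N with larger schools and infer a greater loss; but 1894 is the count before dropout, and the plan's own effective N is 306.

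**What to change.** - Set m to the expected number of participating students per school, after consent, and allow for variation in school size.
- State the level to which the ICC of 0.05 refers. If several grades per school are expected, state the correlation assumed between grades.
- Recompute the design effect and restate the power.
- Give the target as a minimum number of schools per arm as well as a number of students, derived after the base N of 306 has been corrected.

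Do not adopt 24 schools as the target. That figure is only 1894 / 80 and inherits 306; with 1052 in its place, m = 80 would need 1052 × 4.95 / 80 = 65 analysed schools. Do not restrict the data to one grade per school either. At a given number of schools, further students do not reduce precision, and a one-grade rule would turn grade into a school-level factor and weaken the planned comparison of younger and older students.

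The cost is a revised paragraph and a recruitment rule before randomisation. The downside is that the stated power may become less favourable.

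### The sample size uses an average cluster of 80 and sets no number of schools, so unequal school sizes and few school-level degrees of freedom leave the stated power of 0.9 not assured

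*Protocol article*

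**What the plan says.** The Protocol article, Sample size {14}, starts from a small effect: "Assuming a small effect size (Cohens *d* = 0.2) in universal prevention based on previous studies", "with a significance level alpha = 0.05 and a power = 0.9". From this, "g*power suggests a total of *N* = 306". That total is multiplied by 1 + (m − 1) × p, where m is the average number of students per cluster and p is the intraclass correlation. For m, "we assumed an average of 80 within an entire grade as the average class size in Germany varies nationwide"; for the correlation, "the ICC was estimated quite conservatively at approximately 0.05". The factor is 4.95, giving 1515. A 25% addition for dropout gives the final 1894.

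Three other sections bear on m. Sequence generation {16a} randomises schools 1:1. Under Recruitment {15}, a participating school signs a letter "stating how many grades and classes will participate in" the programme, with grades 6 to 12 eligible. Study setting {9} says: "The number of participating schools or classes cannot be predicted at this stage". The Discussion then relies on the adjusted case number to say that small effects would show if they exist.

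**The concern.** The factor 1 + (m − 1) × ICC is exact only when all clusters have the same size. Here each school sets its own size, and nothing holds it near 80 or near one grade. For a fixed total, unequal clusters carry less information than equal ones.

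Multiplying an individual-level N by a design effect also treats the arm comparison as if it had hundreds of degrees of freedom. With schools randomised, it has roughly the number of schools minus 2, and the target is expressed only in students.

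So the trial could reach 1894 students and still have less power than stated, with nothing in the plan to show it. Power 0.9 and the Discussion's remark on small effects both rest on this adjustment.

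**Working it through.** **The plan's own chain.** Design effect: 1 + (80 − 1) × 0.05 = 4.95. Then 306 × 4.95 = 1514.7, rounded to 1515; 1515 × 0.25 = 378.75, rounded to 379; 1515 + 379 = 1894. From 306 onward the arithmetic reproduces.

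**The base N.** The 306 does not follow from the stated inputs for a two-group comparison. The total is 4 × (1.960 + 1.2816)² / 0.2² ≈ 1051, or 1052 with equal arms; the exact t calculation gives 1054, two-sided. With 306 in total, power at d = 0.2 is about 0.41 before any clustering. To isolate the cluster question, 306 is accepted below as giving 0.9.

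**Formulas.**
- DE = 1 + ((1 + CV²) × m − 1) × ICC
- Effective N = analysed N / DE
- Noncentrality = (1.960 + 1.2816) × √(effective N / 306)
- Power from the noncentral t with (schools − 2) degrees of freedom, two-sided 0.05 (the protocol does not state sidedness)

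**Assumed CVs.** The protocol gives none. A uniform spread of 2 to 4 classes per school gives 0.27, and 1 to 6 classes gives 0.49. The values 0 and 0.6 bracket these.

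**Reading A: 80 analysed per school.** The order of the calculation implies this, since 4.95 is applied before dropout is added. 1515 / 80 = 18.9, so about 19 schools and 17 df.

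| CV | DE | Effective N | Noncentrality | Power |
|---|---|---|---|---|
| 0 | 4.95 | 306.1 | 3.24 | 0.86 |
| 0.27 | 5.24 | 289.0 | 3.15 | 0.84 |
| 0.49 | 5.91 | 256.3 | 2.97 | 0.80 |
| 0.6 | 6.39 | 237.1 | 2.85 | 0.77 |

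**Reading B: 80 enrolled per school.** 1894 / 80 = 23.7, so 24 schools and 22 df. After 25% loss within schools, 1894 × 0.75 ≈ 1420 are analysed, about 59 per school.

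| CV | DE | Effective N | Noncentrality | Power |
|---|---|---|---|---|
| 0 | 3.91 | 363.4 | 3.53 | 0.92 |
| 0.27 | 4.13 | 344.4 | 3.44 | 0.91 |
| 0.49 | 4.62 | 307.5 | 3.25 | 0.87 |
| 0.6 | 4.97 | 285.5 | 3.13 | 0.85 |

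**Two grades per school, equal sizes.** With 160 analysed per school, 1515 / 160 ≈ 9.5, so about 9 schools. DE = 1 + 159 × 0.05 = 8.95, effective N = 1515 / 8.95 = 169.3 and noncentrality = 2.41. Power is about 0.53 to 0.56, depending on how the 9.5 is rounded. If 160 is the enrolled size, there are 1894 / 160 ≈ 12 schools with about 118 analysed each (DE 6.87, effective N 206.8, 10 df), and power is about 0.67. Both figures assume that the ICC of 0.05 also applies between students of different grades in one school; a lower value there would soften the loss.

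**The case against.** The factor 4.95 is correct for the inputs given. An average-m design effect is common in a condensed article, and Study setting {9} openly says the number of schools is unknown and why. No CV is documented. The one spread quoted, 21.2 to 30.4 students per class, describes average class sizes and is small: if uniform, its CV is about (9.2 / √12) / 25.8 = 0.10. All of this stands. The loss is therefore conditional on an assumption, and the omission is not a slip in multiplication.

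A reader might go further and infer that 0.9 is certainly missed, whatever is assumed. The documents do not support that: with 80 enrolled in each of 24 schools, power is 0.92 with equal sizes and 0.91 at CV 0.27. Smaller analysed clusters lower the design effect to 3.91, which more than pays for the few degrees of freedom. Pairing 22 df (24 schools, 80 enrolled) with a design effect of 4.95 (80 analysed, about 19 schools) would mix two incompatible readings and overstate the loss for 24 schools.

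Nor can a normal approximation be attributed to the protocol. It cites G*Power without naming the test. What can be said is that inflating an individual-level N leaves out the school-level degrees of freedom.

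Finally, because 306 is unsound, restating 90% as some figure in the 80s could falsely reassure. That is a reason to correct the base N first; correcting it alone would leave the cluster adjustment as it is.

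**Conclusion.** The point holds in conditional form. The sample size fixes m as one grade while the recruitment rule lets each school choose its own size, and no number of schools is set. Power 0.9 is therefore not assured, even with 306 accepted.

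On the reading that the calculation's order implies, it is missed already with equal sizes (0.86). On the more favourable reading, it is met up to about CV 0.27 and missed clearly from about 0.5. The largest exposure is schools entering several grades: the student target would be met while power falls to between one half and two thirds.

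These figures rest on assumed CVs, an ICC of 0.05 at school level and a two-sided test. They show the effect of the cluster adjustment alone and are not the trial's power at d = 0.2, which is far lower because of the base N.

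**What to change.** Correct the base N first. Then recompute with DE = 1 + ((1 + CV²) × m − 1) × ICC over a stated range of CV, with m defined as students per school and stated as enrolled or analysed, and with a t reference on (schools − 2) degrees of freedom. Report the power that the planned N delivers across that range, and qualify the Discussion's statement about small effects to match.

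State the target as a number of schools as well as of students. Ask schools to enter a similar number of classes, for example one grade, as m = 80 already assumes.

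The cost is a recalculation, a less favourable stated power and possibly approaching a few more schools.

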## Trial design {8}

The *LessStress* trial is designed as a cluster-randomised, controlled, non-blinded superiority trial with two parallel groups and a primary endpoint of self-perceived stress after 6 months. We will perform a random assignment on the school level with a 1:1 allocation ratio. The study will last for 6 months and will include four measurement time points: Pre = baseline, Post = student and teacher evaluation, T2 = 3-month follow-up, and T3 = 6-month follow-up (Fig. 1).

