## Statistical methods

### Statistical methods for primary and secondary outcomes {20a}

The intervention group will be compared to the waiting list control group in terms of the difference in change. The data structure will be clustered at different levels (school type, school, grade, class, student), and we must take this into account. To check for the impact of levels, the ICC will be calculated. If the ICC is bigger than 0.1, we will analyse the data using (general) multilevel models. If not, mixed ANOVAS will be performed. First, a null model will be built consisting of the dependent variable and the random intercept. The model fit will be given using the Akaike information criterion AIC. Based on the null model, the independent variables of interest will be included, for the primary outcome self-perceived stress (measured with the PSS-10) and for the secondary outcomes the remaining measure (DERS-SF, SCS, ISI, PHQ-4, CD-RISC, SEED, DSHI-6, SISE, WHO-5, protective factors, FAS III). The AIC will be used to compare the models to one another.

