## Discussion

According to the latest figures, over 20 million people in Germany are affected by mental illness (prevalence of 27.8%), including 2.7 million children and adolescents [92]. The goal of universal prevention is to increase competencies within a large population without prior selection. We want to contribute to this through the prevention programme *LessStress*. The advantages of *LessStress* lie in its short implementation time, the integration into normal school lessons, and the easy training of already existing school staff. If effects can be proven, a step would be taken towards keeping children and adolescents healthy in the school setting. If *LessStress* does not prove to be effective, it is important to find out what we can improve to bring scientifically evaluated and effective prevention programmes into schools. At the same time, some of the benefits of *LessStress* should also be seen as limitations. In particular, the short implementation time and the implementation by teachers may influence our outcomes. Moreover, the different schools with different requirements for the students could have a negative impact on this study. However, with our adjusted case number estimation, even small effects will be visible, insofar as they exist.

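### The starting N = 306 is not the size of a two-group comparison at d = 0.2 with 90% power (that is 1054), so 1894 students give about 40–50% unadjusted two-sided power

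*Protocol article*

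**What the plan says.** All references are to the protocol article.

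- **Trial design {8}** describes a "cluster-randomised, controlled, non-blinded superiority trial with two parallel groups and a primary endpoint of self-perceived stress after 6 months".
- **Sequence generation {16a}**: "The randomisation will be carried out on the school level following a 1:1 allocation ratio".
- **Statistical methods for primary and secondary outcomes {20a}** fixes the contrast as one between groups: "The intervention group will be compared to the waiting list control group in terms of the difference in change".
- **Sample size {14}**: "Assuming a small effect size (Cohens *d* = 0.2) in universal prevention based on previous studies", and then "with a significance level alpha = 0.05 and a power = 0.9, g*power suggests a total of *N* = 306". The section sets the average cluster size at 80 and the ICC at about 0.05, which gives a design effect of 4.95. It multiplies 306 by 4.95 to get 1515 and adds 379 for 25% dropout to reach 1894. It names no test, sidedness, number of repeated measures or pre-post correlation.
- **Discussion**: "However, with our adjusted case number estimation, even small effects will be visible, insofar as they exist".

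**The concern.** The contrast of interest is between two randomised groups. A standardised difference of 0.2 with 90% power needs over a thousand individually randomised students, and 306 is less than a third of that. The design effect and the dropout allowance only scale this base, so the shortfall carries through to 1894.

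The headline power is at stake. A reader who accepts 90% power for d = 0.2 would take a non-significant result as evidence that this short universal programme has no small benefit, and the Discussion invites that reading. With the power actually available, such a result would say much less.

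**Working it through.** **Inputs.** From Sample size {14}: d = 0.2, alpha 0.05, power 0.90, m = 80, ICC = 0.05, dropout 25%. From Trial design {8} and Sequence generation {16a}: two groups, 1:1. Sidedness is not stated, so two-sided is assumed here and one-sided is shown beside it.

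**1. The protocol's later steps reproduce.**
- Design effect: 1 + (80 − 1) × 0.05 = 4.95
- 306 × 4.95 = 1514.7, rounded to 1515
- 1515 × 0.25 = 378.75, rounded to 379; 1515 + 379 = 1894

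**2. The starting figure does not.**
- Per group, two-sided: 2 × (1.96 + 1.2816)² / 0.2² = 525.4. The exact t-test needs 527, so the total is 1054.
- One-sided: 858 in total.
- At 80% power: 786 two-sided, 620 one-sided.

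306 students in two groups have about 42% power at d = 0.2 (54% one-sided). They reach 90% only at d = 3.2415 × √(4/306) = 0.37.

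**3. What 1894 recruited students deliver at d = 0.2.** Effective N = analysed N / design effect. Power is for an unadjusted comparison. The d detectable with 90% power is 2 × 3.2415 / √(effective N).

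| Scenario | Analysed | Design effect | Effective N | Two-sided power | d at 90% power |
|---|---|---|---|---|---|
| 25% lost, 80 per cluster kept | 1420.5 | 4.95 | 287 | 39.5% | 0.38 |
| 25% lost, 60 per cluster left | 1420.5 | 1 + 59 × 0.05 = 3.95 | 360 | 47.5% | 0.34 |
| No loss | 1894 | 4.95 | 383 | 49.8% | 0.33 |

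With a t reference based on the number of clusters (1420.5/80 ≈ 18 to 1894/80 ≈ 24), power at 80 per cluster is 36–46%. One-sided, with 80 per cluster, it is 52–62%.

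**4. Could baseline adjustment justify 306?**
- Analysis of covariance: 1 − r² = 306/1054 = 0.290, so r ≈ 0.84.
- Change score: 2(1 − r) = 0.290, so r ≈ 0.85.

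No correlation is stated. A six-month correlation of 0.84 would equal the internal consistency quoted for the PSS-10 (0.84), which is hard to credit. At assumed values, over 1420.5 to 1894 analysed and a design effect of 4.95:

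| Assumed r | Analysis of covariance | Change score |
|---|---|---|
| 0.5 | 50–62% | 40–50% |
| 0.7 | 66–78% | 59–71% |

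**5. Other routes to 306.** These were tried and none gives 306 for the stated contrast.
- A one-group paired t-test needs 265, and a paired Wilcoxon test at its worst-case efficiency about 307. Both are within-group tests.
- A repeated-measures group-by-time interaction with f = 0.1, three measures and correlation 0.3 gives 298. It needs unstated inputs, and f = 0.1 is a different effect: with two measures it is a 0.4 SD difference in change.

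The document does not show where 306 came from.

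**6. Size implied by the stated inputs.** 1054 × 4.95 = 5217 analysed. By the protocol's own dropout convention, 5217 × 1.25 ≈ 6522 recruited; dividing by 0.75 instead gives about 6957.

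**The case against.** The strongest reply is that 39–50% describes an unadjusted, two-sided comparison at one time point, whereas the protocol plans to compare change and uses multilevel models or mixed ANOVA. With a useful baseline correlation the trial is not more likely than not to miss d = 0.2. That is fair, and the power figures must carry their conditions. It does not restore 90%: a plain change score gains nothing at r = 0.5. With analysis of covariance, r = 0.8 reaches 90% only if nobody is lost (81% with 25% lost).

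The ICC of 0.05 is also described as conservative. If it were 0.02 (an assumption), the design effect would be 1 + 79 × 0.02 = 2.58, or 2.18 with 60 per cluster. Unadjusted power with 1420.5 analysed would then be about 65–72%, and 77–84% at r = 0.5. A low ICC combined with r = 0.7 could get there: 1420.5 / 2.58 / (1 − 0.49) ≈ 1080 effective, about 91% power. So the trial may do better than its planning values suggest, but neither value is in the protocol and the calculation does not rest on them.

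Two further points stand. The origin of 306 should not be asserted. And treating all 25% as lost is pessimistic, since only students missing more than one follow-up are excluded and multiple imputation is planned. The no-loss row above covers that case and still gives about 50%.

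An unseen analysis plan cannot settle the matter, because the article prints both the inputs and a result, and they disagree for the design that it describes.

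**Conclusion.** The concern holds. On the stated d, alpha and power, a two-group comparison needs 1054 students before clustering (858 one-sided). The protocol's 306 is too small by a factor of about 3.4 (1054/306). At the protocol's own ICC, cluster size and dropout, the effective N is 287 to 383, unadjusted two-sided power is 39–50%, and the effect detectable with 90% power is d of about 0.33–0.38.

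These figures are conditional on ICC 0.05 and no baseline adjustment. Varying sidedness, or assuming r of 0.5–0.7 at that ICC, raises power but leaves it below 90%. The 90% claim and the Discussion sentence that relies on it are unsupported as written and must be corrected.

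**What to change.** In Sample size {14}:

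- Replace 306 by 1054 as the individually randomised total, and name the test and its sidedness (858 if one-sided is intended).
- Say openly that carrying 1054 through the section's own steps gives about 5217 analysed and about 6522 recruited. If 1894 is kept, present it as the chosen target and not as the product of that chain.
- Restate what 1894 delivers: about 40–47% unadjusted two-sided power for d = 0.2 after 25% dropout (about 50% with none), or 90% power for d of about 0.34–0.38 after dropout.
- If the design relies on baseline adjustment or a lower ICC, state the assumed values, their basis and the resulting power.

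In the Discussion, delete the claim that small effects will be visible. Commit to reading a non-significant result from the confidence interval for the group difference.

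The cost is protocol wording only. The stated power becomes much less favourable, but no extra enrolment is required.

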**Methods:**

The effectiveness of the short and economical prevention programme *LessStress* will be examined in a cluster-randomised controlled trial (RCT) encompassing 1894 students. At several measurement time points, students from two groups (intervention and control) will be asked about their subjectively perceived stress levels, among other aspects. Due to the clustered nature of the data, mainly multilevel analyses will be performed.

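### The 25% dropout allowance is added to 1515 (giving 1894) rather than divided out (2020), so 1894 covers only 20% dropout; the same section also gives an underived N = 1795

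*Protocol article*

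**What the plan says.** Sample size {14} builds the target in labelled steps.

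- **Base.** "Assuming a small effect size (Cohens *d* = 0.2) in universal prevention based on previous studies", "with a significance level alpha = 0.05 and a power = 0.9", and then "g*power suggests a total of *N* = 306".
- **Clustering.** For the cluster size, "we assumed an average of 80 within an entire grade"; the ICC is about 0.05. The resulting factor of 4.95 is multiplied into 306 to give 1515.
- **Dropout.** "Assuming a dropout rate of 25% due to moving out of the area, sickness, or other reasons, we must add another 379", which gives the final N of 1894.

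The Methods part of the abstract repeats that target ("cluster-randomised controlled trial (RCT) encompassing 1894 students"), as does the Aims section.

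Earlier in the same section, before the inputs are listed, the clustering adjustment is said to have "resulted in an estimated *N* = 1795". That figure is not derived and is not used again.

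**The concern.** A dropout rate is a share of the students enrolled, but the section applies it as a share of the students needed at the end. The two differ: to keep n students after losing a fraction d, one must enrol n/(1 − d), not n × (1 + d). If the stated 25% occurs, the stated 1894 does not deliver the stated 1515. The rate, the requirement and the target cannot all hold.

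What is at stake is the headline recruitment figure, and with it the number expected at analysis. The Discussion relies on the adjusted sample size when it says that even small effects will be detectable.

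The 1795 adds a second difficulty. The section attributes it to the clustering step and later attributes 1515 to that same step, so a reader cannot tell which calculation was carried out.

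**Working it through.** **Inputs, all from Sample size {14}:** base total 306; cluster size m = 80; ICC 0.05; dropout 25%; alpha 0.05; power 0.90. Sidedness is not stated. Allocation is 1:1 by school (Trial design {8}).

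**1. Reproducing the plan's figure**
- Design effect: 1 + (80 − 1) × 0.05 = 4.95.
- After clustering: 306 × 4.95 = 1514.7, rounded to 1515.
- Dropout as applied: 1515 × 0.25 = 378.75, rounded to 379; 1515 + 379 = 1894.

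The plan's 1894 is reproduced exactly, but only as n × (1 + d).

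**2. What 1894 delivers**
- Completers at 25% dropout: 1894 × 0.75 = 1420.5.
- Shortfall against 1515: 94.5, and 94.5/1515 = 6.2%.
- Dropout at which 1515 remain: 1 − 1515/1894 = 20.0%.
- Enrolment consistent with 25%: 1515/0.75 = 2020, which is 126 more than 1894.

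**3. Effect on power, taking 306 as giving 90%**

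For a two-sided test, power = Φ(3.2415 × √(effective N/306) − 1.96), where 3.2415 = 1.96 + 1.2816.

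| | m = 80 among analysed students | m = 80 among enrolled students, 25% lost within each grade |
|---|---|---|
| Analysed cluster size | 80 | 80 × 0.75 = 60 |
| Design effect | 4.95 | 1 + 59 × 0.05 = 3.95 |
| Effective N from 1420.5 completers | 287 | 360 |
| Power | Φ(1.18) = 0.88 | Φ(1.55) = 0.94 |
| Completers needed for effective N = 306 | 1515 | 306 × 3.95 = 1209 |
| Enrolment needed at 25% dropout | 2020 | 1209/0.75 = 1612 |

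A one-sided test also gives 0.88 in the first column.

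**4. The stray 1795**

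Working back with the stated design effect:
- with no dropout step, 1795/4.95 = 362.6;
- with × 1.25, 1795/(1.25 × 4.95) = 290.1;
- with division by 0.75, 1795 × 0.75/4.95 = 272.0.

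None of these is 306, and 1795 is not 1515, 1894 or 2020.

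**5. The base of 306**

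For a two-group comparison of means with d = 0.2, alpha 0.05 and power 0.90, the normal approximation gives a total of 1052 two-sided or 858 one-sided. The section names no test that leads to 306. This is a separate and larger matter. It is noted here because 1515, 2020 and every power figure in step 3 rest on 306.

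**The case against.** The strongest reply concerns the design effect. The section describes 80 as the size of a whole grade and justifies it from national class sizes, which reads most naturally as a count before dropout. The loss reasons it gives are individual ones (moving away, sickness), not the loss of whole schools. On that reading clusters shrink to 60, the design effect falls to 3.95, and 1894 is more than enough on the base of 306. This stands as an objection to any unconditional claim of lost power. It does not rescue the arithmetic: the section multiplies by 4.95, calls the result 1515 and adds dropout on top, so its own chain treats 80 as the size among those analysed.

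It can also be said that not every dropout is lost to the analysis. The retention section {18b} excludes a student only when more than one follow-up is missing, and section {20c} plans multiple imputation. This softens the effect by an amount that cannot be computed from the document. Students missing both follow-ups are still excluded.

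Third, even the unfavourable reading costs about two percentage points of power, and the ICC and cluster size are themselves rough. That is fair, and it limits the weight of the point.

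A reader might also infer that the section offers three competing totals. It does not: 1515 and 1894 are labelled successive steps, and 1894 is clearly the operative target. Only 1795 is out of place.

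**Conclusion.** The dropout step is wrong as written. At the stated 25%, 1894 leaves about 1420 completers, roughly 95 (6%) below the protocol's own 1515; 1894 matches 20% dropout, and 2020 matches 25%. These statements need only the section's own figures.

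The consequence for power is conditional. It is about 88% instead of 90% if the design effect remains 4.95 after dropout and 306 is accepted as giving 90%. It is about 94%, with no shortfall, if 80 is the enrolled grade size and losses fall evenly within grades. One might infer that the dropout slip by itself leaves the trial underpowered; the document does not support that, because it does not say which of the two 80 refers to. Nor does it follow that 2020 is an adequate sample size: 2020 repairs the dropout step only and inherits a base that does not reproduce.

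N = 1795 conflicts with the 1515 given for the same step and follows from no stated inputs. The effect is one of clarity, since nothing later depends on it.

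Overall this is a definite error in the trial's headline number, modest in its own effect, that should be corrected.

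**What to change.** In Sample size {14}:

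1. Either keep 1894 and state that it supports about 1420 completers at 25% dropout (equivalently, 1515 at 20%), or give 2020 as the enrolment consistent with 1515 completers at 25%.
2. State whether the cluster size of 80 counts enrolled or analysed students, and use the matching design effect.
3. Recheck the base of 306, naming the test and its inputs, and then restate power for the expected number of completers. Apply the dropout step as division by 0.75 to whatever base results.
4. Delete N = 1795.

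If 1894 is kept, items 1, 2 and 4 are changes of wording, and the abstract and Aims need no change. Choosing 2020 means recruiting 126 more students and updating both of those places. Item 3 is a desk calculation; any change in sample size that follows from it belongs to the separate question of the base figure.
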